
Subjective psychopathological symptoms will be assessed with the German translation (115) of the Brief Symptom Inventory (BSI) (116). The BSI measures psychopathology based on the following nine syndromes: somatization, obsessive–compulsive, interpersonal sensitivity, depression, anxiety, hostility, phobia, paranoia, and psychoticism. Although these scales demonstrated good reliability (115, 116), due to rather poor convergent and discriminant validity, it has been suggested to use only the total impairment score (117). As an alternative measure of subjective impairment we will use the incongruence questionnaire (INK) (118). The INK measures motivational incongruence, defined as the discrepancy between a person’s motivational goals and his/her perception of the actual fulfilment of his/her socio-affective needs. The INK has shown good psychometric properties and correlates strongly with psychopathological distress, which makes it a valuable tool for treatment evaluation in psychotherapy research and practice (118, 119). Finally, the treating psychotherapist will quantify the global functioning of the patient using the Global Assessment of Functioning (GAF) scale (120) in order to obtain an objective other rating of his/her psychopathological impairment. All measures of psychopathology, that is, BSI, INK, and GAF will be administered both at baseline and 6-month follow-up. In addition to the inventories and rating scales detailed above, information from the patient chart, including diagnoses according to ICD-10, age, sex, and education level, will also be recorded in the dataset. The flowchart is shown in Figure 1.

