(1)BFI traits show high differential continuity over time (all *r* > 0.6). To test this prediction, we will compute bivariate Pearson correlations between trait scores at baseline and 6-month follow-up. We will provide both attenuated and disattenuated correlation coefficients corrected for scale unreliability.(2)BFI traits demonstrate substantial mean-level continuity (all *d* < 0.5). More specifically, we predict that only neuroticism will demonstrate modest mean-level change (0.2 < *d* > 0.5), while the other four traits will remain almost unaltered over time (all *d* < 0.2). These predictions will be tested with *t*-tests for paired samples by examining the differences in standardized mean-level change between baseline and 6-month follow-up.(3)Baseline BFI traits, specifically high neuroticism and low conscientiousness, substantially reduce (*d* > 0.5) the effectiveness of psychotherapy based on the BSI, GAF, and INK over the 6-month observation period. In order to test this prediction, we will compute GEE (121). These statistical models were introduced to fit regression analyses that account for within-subject correlation, which is an inherent part of longitudinal studies that rely on repeated outcome measures. Together with mixed models and random coefficient models, GEE represent the state of the art for longitudinal data analysis and are preferred to repeated measures ANOVA due to their superior psychometric properties (122, 123). The baseline BFI traits will be entered as the predictor variables and the repeated measures of the BSI, GAF, and INK successively as the outcome. The effect size of interest will be modeled as the interaction term between baseline personality and the time slope coefficient of the repeated outcomes, that is, the linear time trend for change in BSI, GAF, and INK. By simultaneously adjusting for the intercept, such a statistical modeling ensures that change in psychopathology over time is estimated independent of baseline impairment. These models will be conducted with and without adjustment for baseline diagnoses based on ICD-10.(4)Mean-level change in BFI traits is only weakly, if at all, correlated with change in psychopathological impairment over time (all *r* < 0.3). To test this hypothesis, we will compute individual change scores over time for all repeated measures by subtracting the baseline score from the follow-up score. The change scores of the BFI traits will then be correlated with the change scores of the BSI, GAF, and INK using Pearson correlation.

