
Second paper: the second confirmatory analysis will focus on the IIP and IMI-C. We will test the following hypotheses:
(1)Self-reports and informant ratings of interpersonal personality problems are only modestly correlated (all *r* < 0.3). To test this hypothesis, we will subject the IIP (self-report) and the IMI-C (informant rating) to a bivariate Pearson correlation analysis.(2)Both self-reported and informant-rated baseline personality problems according to the IIP and IMI-C substantially reduce (*d* > 0.5) the effectiveness of psychotherapy according to change in BSI, GAF, and INK from baseline to 6-month follow-up. As specified above with respect to the BFI, we will test these predictions by focusing on the interaction effect between baseline personality measures and the time slope coefficients of the psychopathology outcomes using a series of GEE analyses.(3)Self-other agreement in personality profiles relates stronger to the outcome of psychotherapy than either self-report (IIP) or informant rating (IMI-C). To test this hypothesis, we will first compute the index of profile agreement (*I*_pa_) between IIP and IMI-C as recommended by McCrae (124) and then compare the slope-interaction effect of the *I*_pa_ with the multivariable effects obtained for the IIP and the IMI-C domains based on the results of GEE as specified above. The difference between two effect sizes will be considered statistically significant if the 95% confidence intervals of their standardized regression coefficients do not overlap.(4)IIP and IMI-C have substantial incremental criterion validity (Δ*R*^2^ > 0.05) above and beyond each other in the prediction of the outcome of psychotherapy. This hypothesis will be tested by subjecting the change scores over time for BSI, GAF, and INK to a hierarchical linear regression analysis, where baseline IIP and IMI-C are entered in interchangeable hierarchical blocks as the predictor variables. In these models, the effect size of interest will be the amount of additional variance explained (Δ*R*^2^) accounted for by either IIP or IMI-C in the prediction of intraindividual change in BSI, GAF, and INK over time.

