### Caveats and Potential Pitfalls

We have stressed that clinical trials in psychotherapy and psychopharmacology commonly have poor external validity, that is, the efficacy of treatments for mental disorders as estimated in the laboratory under controlled conditions using selective samples only poorly corresponds to real-world effectiveness in unselected naturalistic samples (47, 48). On the other hand, clinical trials have considerably higher internal validity than observational studies, which is why they are considered the gold standard for the estimation of causal effects. That holds particularly true when the main objective is to evaluate the efficacy of a given intervention. Observational studies are merely correlational, as interventions cannot be randomly assigned to participants. Therefore, they do not allow for strict causal conclusions, although sophisticated statistical techniques such as propensity score matching can approximate the internal validity of observational designs to that of randomized experiments (125). However, as we are mainly interested in the longitudinal covariance between personality and psychopathology and in the stability of personality, but not on the efficacy of psychotherapy as an intervention *per se*, that potential limitation is not at issue. That is, we are not interested in testing the efficacy of an intervention, but rather in evaluating possible mechanisms operating within that particular intervention. We will therefore not apply propensity score matching, as we do not compare psychotherapy users with untreated patients or other treatment modalities. A bias that needs to be addressed in such a study is the content overlap between personality and psychopathology, in particular that between neuroticism and depression (126), as that bias might artificially inflate the association between these constructs. To solve that problem, we will apply outcomes such as the GAF and the INK that have no content overlap with neuroticism. Moreover, we will also use alternative measures of personality such as the circumplex model of personality problems, which will be assessed based on both self-report and informant rating. Finally, though we consider the heterogeneity of this representative sample a particular strength, one might also argue that we compare apples to oranges. That argument holds particularly true with respect to interindividual differences in baseline impairment. As detailed above, we will resolve that issue by applying statistical models that estimate the change in psychopathology over time while holding baseline impairment constant. In order to additionally control for distinct baseline psychopathology, we will also include a patient’s primary diagnosis as a covariate.

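### The personality-by-time GEE term measures unadjusted change and does not hold baseline impairment constant, as the plan says it does

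*Protocol article*

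**What the plan says.** Under Hypotheses and Planned Analyses (first paper, hypothesis 3), the model is set out as follows: "The baseline BFI traits will be entered as the predictor variables and the repeated measures of the BSI, GAF, and INK successively as the outcome". Its tested parameter is also named: "The effect size of interest will be modeled as the interaction term between baseline personality and the time slope coefficient of the repeated outcomes". The plan then claims: "By simultaneously adjusting for the intercept, such a statistical modeling ensures that change in psychopathology over time is estimated independent of baseline impairment".

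Caveats and Potential Pitfalls relies on this property. It raises the objection that very different patients are being compared, above all in how impaired they are at the start, and says the objection is met by "applying statistical models that estimate the change in psychopathology over time while holding baseline impairment constant". Diagnosis is the second safeguard. The hypothesis section says "These models will be conducted with and without adjustment for baseline diagnoses based on ICD-10", and the caveats section lists the "primary diagnosis as a covariate".

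There are only two occasions. Instruments and Measures states: "All measures of psychopathology, that is, BSI, INK, and GAF will be administered both at baseline and 6-month follow-up". Study Site and Sampling Procedure drops the 12-month assessment. Hypotheses 2 and 3 of the second paper reuse the same interaction for the IIP, the IMI-C and the profile-agreement index.

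**The concern.** A GEE has one population intercept, not one per patient. Together with the trait main effect it describes the average baseline level at each trait value. It does not compare patients who start equally impaired. The baseline score sits on the outcome side, and the article names no term that conditions on it.

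The distinction matters because the article's introduction says that high neuroticism and low conscientiousness are strongly related to psychopathology. If so, trait and baseline impairment are correlated. The association of the trait with change and its effect at equal baseline are then different quantities, and they can differ in sign. A reader told that baseline was held constant would take the first for the second. The plan's answer to its own objection about unlike patients would then rest on a property that the model lacks.

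**Working it through.** The plan gives no figure for this point, so there is none to reproduce. Its sample size does not bear on it.

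**1. What the interaction is.** Code time T as 0 at baseline and 1 at 6 months, and let P be the trait:

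E(Y) = a + b1·P + b2·T + b3·P·T

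At T = 0 the slope on P is b1. At T = 1 it is b1 + b3. So in complete pairs b3 is the slope of (Y1 - Y0) on P. In one simulated data set of 100 complete pairs:

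| Model | Coefficient |
|---|---|
| GEE, trait × time, independence or exchangeable | -0.10909 (SE 0.1129) |
| OLS of change score on trait | -0.10909 |
| 6-month score on trait and baseline score | +0.08856 |

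The first two are identical. The third, which does hold baseline constant, has the opposite sign in these data.

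**2. Size of the difference.** Take unit SDs and an outcome scored so that higher is worse. Let b be the trait effect on Y1 at equal Y0, s the slope of Y1 on Y0 given the trait, and rho0 the trait-baseline correlation:

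interaction = b + s·rho0 - rho0 = b - (1 - s)·rho0

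The article gives neither rho0 nor s, so both are assumed.

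- rho0 = 0.2, s = 0.7: shift = -0.3 × 0.2 = -0.06
- rho0 = 0.5, s = 0.5: shift = -0.5 × 0.5 = -0.25
- rho0 = 0.6, s = 0.4: shift = -0.6 × 0.6 = -0.36
- rho0 = 0: no shift

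For scale, the hypothesised d = 0.5 converts to r = 0.5/√(0.5² + 4) = 0.2425.

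**3. Consequence if the target is the effect at equal baseline.** These are 4,000 simulated trials of n = 100 per scenario, with complete pairs:

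| rho0, s | True b | GEE term: mean; significant | Baseline-adjusted: significant |
|---|---|---|---|
| 0.5, 0.5 | 0.2425 | -0.01; 3% in the hypothesised direction | 79% in the hypothesised direction |
| 0.5, 0.5 | 0 | -0.25; 73% in the opposite direction | about 2.5% in each direction |
| 0.3, 0.7 | 0.2425 | 0.15; 65% in the hypothesised direction | 96% in the hypothesised direction |

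**4. The mirror case.** Let the trait correlate 0.5 with both scores, and let the scores correlate 0.6 with each other. The interaction is 0.5 - 0.5 = 0. The baseline-adjusted coefficient is (0.5 - 0.6 × 0.5)/(1 - 0.5²) = 0.20/0.75 = +0.27. In 4,000 simulated trials of n = 100, the interaction was significant in 4.9%. The baseline-adjusted model was significant in the hypothesised direction in 84%.

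**5. Diagnosis.** A time-invariant main effect cancels from Y1 - Y0. In the complete-pair data of step 1, adding diagnosis as a main effect left trait × time at -0.10909 with the same SE. Adding diagnosis × time moved it to -0.04870. With baseline-only patients kept (150 baselines, 89 followed up), a diagnosis main effect did move the term: from -0.485 to -0.418 under independence, and from -0.414 to -0.382 under an exchangeable structure. Even then no baseline score is conditioned on.

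**The case against.** The strongest reply is that in a non-randomised study the choice between change and baseline-adjusted analysis is a choice of estimand. Hypothesis 3 speaks of effectiveness over the observation period and of a time trend for change. Hypothesis 2 of the second paper likewise refers to change. The interaction estimates that quantity, and only the two sentences about baseline impairment promise something else. This stands, and it limits the point to a false description and an unstated target.

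A reader might infer that regression to the mean has been shown to bias the test. The documents do not support that. The results in step 3 fix the truth at equal baseline, which favours baseline adjustment by construction. Step 4 fixes it the other way, and there the adjusted model errs in favour of the hypothesis. As a measure of change in underlying severity, the interaction is distorted only if the trait score shares the transient part of the baseline outcome. In a measurement-error check, a trait tied only to stable severity gave an interaction of about 0 and an adjusted coefficient of 0.17. A trait also tied to the transient part gave -0.15 and 0.04. Sharing is plausible for self-reported neuroticism with the BSI or INK, and less so for the therapist-rated GAF or the informant-rated IMI-C. The article cannot settle which case applies.

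A reader might also infer that adjusting for diagnosis can never matter. That holds only for a main effect in complete pairs. The article does not say how diagnosis enters, and patients whose therapy ends early have a baseline only, which a GEE can keep.

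Finally, hypothesis 4 of the second paper also works by "subjecting the change scores over time for BSI, GAF, and INK to a hierarchical linear regression analysis". It expressly targets change within individuals and makes no claim there about holding baseline constant, so it does not share the error.

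**Conclusion.** The two statements about baseline impairment are wrong for the model described. This needs no assumption beyond the two occasions and the terms that the article names. The same term carries over to hypotheses 2 and 3 of the second paper.

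The gap between what is estimated and what is claimed is -0.06 to -0.36 SD per trait SD over the assumed ranges, and zero if trait and baseline impairment are uncorrelated. For neuroticism it works against hypothesis 3, so relative to the stated target it would hide an effect rather than create one.

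The documents do not support calling this proven bias in unconditional change, nor making the baseline-adjusted model a mandatory replacement. They also designate none of the hypotheses as the main one. If diagnosis enters only as a main effect, the comparison with and without it tests nothing in complete pairs.

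**What to change.** 1. Delete or correct the two claims, in hypothesis 3 of the first paper and in the caveats section. State for each hypothesis whether it targets unadjusted change or the effect at equal baseline impairment.
2. For hypothesis 3 of the first paper and hypotheses 2 and 3 of the second, prespecify a regression of the 6-month score on the trait (or the corresponding personality measure), the baseline score of the same outcome, and diagnosis. Report it next to the GEE interaction, and label the latter unadjusted change. Claim that baseline impairment is held constant only from the regression.
3. Enter diagnosis with its time interaction in the adjusted GEE.
4. A baseline block in hypothesis 4 of the second paper is optional.

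The cost is wording and a few more models, since every variable is already collected. The downside is two estimates that may disagree. Measurement error in the baseline score can also leave residual confounding or bias in the adjusted model, which step 4 of the working shows need not be small. The plan should therefore say in advance how a disagreement will be read.

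### Paper 1, hypothesis 4 calls the trait–symptom change link weak on raw difference scores, so measurement error could help to confirm it

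*Protocol article*

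**What the plan says.** All relevant text is in the Protocol article, Hypotheses and Planned Analyses.

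- **Paper 1, hypothesis 1** predicts baseline to 6-month trait correlations above 0.6, so a high value confirms. It adds: "We will provide both attenuated and disattenuated correlation coefficients corrected for scale unreliability". It does not say which of the two coefficients is compared with 0.6.
- **Paper 1, hypothesis 4** predicts that mean-level change in BFI traits "is only weakly, if at all, correlated with change in psychopathological impairment over time (all *r* < 0.3"), so low values confirm. The method is fixed: "we will compute individual change scores over time for all repeated measures by subtracting the baseline score from the follow-up score", and then "The change scores of the BFI traits will then be correlated with the change scores of the BSI, GAF, and INK using Pearson correlation". No correction is named.
- **Paper 2, hypothesis 1** also predicts correlations below 0.3, here between self-report and informant rating. The test is again uncorrected: "we will subject the IIP (self-report) and the IMI-C (informant rating) to a bivariate Pearson correlation analysis".

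Instruments and Measures describes the BFI and the BSI scales as reliable but gives no coefficient. The Summary and Conclusion says that the exact analyses are prespecified in this article.

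**The concern.** Random error pulls a correlation towards zero. Where a hypothesis is confirmed by a low correlation, unreliability works in its favour. Hypothesis 4 is the most exposed, because it correlates simple differences of traits that the same paper predicts to be stable. For a given scale reliability, the more stable the trait, the larger the share of the observed difference that is error. Support for hypothesis 1 therefore tends to help hypothesis 4 as well, apart from any real relation between trait change and symptom change.

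The association between change in psychopathology and change in personality is the third aim in the Abstract. At stake is whether a moderate association could be published as a confirmed weak one.

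**Working it through.** **Inputs from the article:** thresholds 0.6 and 0.3; raw differences; plain Pearson r; about n = 100 follow-up assessments; 5 traits × 3 outcomes = 15 correlations. The plan has no calculated figure on this point to reproduce.

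**Assumed inputs, since the article gives none:** BFI reliability 0.75–0.85 and observed stability 0.60–0.70; outcome reliability 0.90–0.95 and stability 0.60. Equal variances at both times and uncorrelated errors are assumed.

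**Step 1. Reliability of a difference score** = (reliability − stability) / (1 − stability).
- BFI, lowest: (0.75 − 0.70)/0.30 = 0.17
- BFI, highest: (0.85 − 0.60)/0.40 = 0.63
- BFI at 0.80 and 0.70: 0.10/0.30 = 0.33
- BFI at 0.80 and the plan's own 0.60: 0.20/0.40 = 0.50
- Outcome: (0.90 − 0.60)/0.40 = 0.75, to (0.95 − 0.60)/0.40 = 0.875

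**Step 2. Attenuation** = √(BFI change reliability × outcome change reliability). The error-free r behind an observed 0.30 is 0.30/attenuation.
- Worst corner: √(0.167 × 0.75) = 0.354; 0.30/0.354 = 0.85
- Best corner: √(0.625 × 0.875) = 0.74; 0.30/0.74 = 0.41
- BFI 0.80 and 0.70: attenuation 0.50–0.54; error-free r 0.56–0.60
- BFI 0.80 and 0.60, with outcome change reliability 0.80 or 0.50: 0.47 or 0.60

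A second grid, with BFI reliability 0.75–0.90 at stability 0.60 and outcome change reliability 0.4–0.9, gives 0.37–0.77.

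**Step 3. Chance that one correlation passes at n = 100** (Fisher z, standard error 1/√97). Take an error-free r of 0.50.
- Both change reliabilities 0.50: expected observed r = 0.25; P(observed r < 0.3) is about 0.70.
- Outcome change reliability 0.80: expected r = 0.32; P is about 0.43.
- No measurement error: P is about 0.009.

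**Step 4. Correlated errors.** Observed r = true r × √(relX × relY) + error correlation × √((1 − relX)(1 − relY)). With both change reliabilities 0.50, a true r of 0.50 and an error correlation of 0.1: 0.25 + 0.1 × 0.50 = 0.30. A small shared error removes part of the attenuation.

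**Step 5. The other two correlation hypotheses.**
- Paper 2, hypothesis 1: 0.30/√(0.80 × 0.80) = 0.375, and 0.33–0.43 for reliabilities 0.90 down to 0.70.
- Paper 1, hypothesis 1: at reliability 0.80 a raw stability of 0.60 × 0.80 = 0.48 becomes 0.60 after correction, so the choice of deciding coefficient can change the answer.

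**The case against.** A reader might infer that correction was placed only where it favours the authors. The article does not support that. Hypothesis 1 reports the raw coefficient as well, so nothing is hidden. Correction is also absent where it would help: in the interaction hypotheses (d > 0.5) and the incremental-validity hypothesis (ΔR² > 0.05). What remains is inconsistent treatment of correlations and an unnamed deciding coefficient.

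A reader might also infer that hypothesis 4 would be confirmed whatever the truth. That is too strong, for three reasons.
- All 15 correlations must fall below 0.3. With a 0.70 chance each, three independent ones would all pass with probability 0.70³ = 0.34, and more often if they are positively dependent.
- In the best corner a true 0.50 is observed at 0.50 × 0.74 = 0.37 and refutes the hypothesis.
- BFI, BSI and INK are self-reports from the same assessments, and Caveats and Potential Pitfalls itself names content overlap as a source of inflation. The net direction of bias for those pairs is not established. The argument has less force for the GAF, which the therapist rates.

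It can also be said that a threshold stated for a plain Pearson r is a claim about observed scores, and that a fuller protocol may add supplementary coefficients. The first is fair if the conclusion is worded that way. The second does not remove the point, because the article fixes the method for hypothesis 4 and describes its analyses as exact.

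**Conclusion.** The point holds for paper 1, hypothesis 4, in a conditional form. With the stated method, an observed change–change correlation of 0.30 could reflect an error-free one of roughly 0.4 or more (0.41–0.85 over the main assumed range), so the hypothesis could be confirmed partly through measurement error. The size rests on assumed reliabilities and stabilities, equal variances and uncorrelated errors; shared error between self-reports may offset part of it.

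Extending the charge to paper 2, hypothesis 1 is tempting but not supported: attenuation there is mild (0.30 becomes about 0.33–0.43), and unreliability alone does not produce the result.

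**What to change.** Extend to paper 1, hypothesis 4 the reporting rule already set for hypothesis 1:

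- Report each change–change correlation raw and corrected for change-score reliability, each with a confidence interval. For BFI, BSI and INK, take reliability from the sample's internal consistencies and retest correlations. For the GAF, described as a global rating by the treating therapist with no items or second rater, show the corrected value over a stated range of assumed reliability.
- Add a sensitivity check for correlated errors between same-occasion self-reports.
- State in advance which coefficient decides in hypotheses 1 and 4.
- Where raw r is below 0.3 but corrected r is not, limit the conclusion to observed scores or call it undetermined, not weak.
- For paper 2, hypothesis 1, a corrected coefficient is an optional supplement.

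**Cost:** some wording and a few lines of analysis, with no new data. Only six follow-ups were complete in October 2016, so at the time of writing the change could still be made in advance.

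**Downside:** corrected intervals are wide. At n = 100 the raw 95% interval around r = 0 is ±0.196; divided by an attenuation of 0.54 or 0.50 it becomes about ±0.36 or ±0.39. Requiring the corrected interval to exclude 0.3 would then make hypothesis 4 impossible to confirm, so that should not be the rule. Even without it, many trait–outcome pairs may end undetermined.

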## Abstract

The role of personality trait variation in psychopathology and its influence on the outcome of psychotherapy is a burgeoning field. However, thus far most findings were based on controlled clinical trials that may only poorly represent real-world clinical settings due to highly selective samples mostly restricted to patients with major depression undergoing antidepressive medication. Focusing on personality and psychopathology in a representative naturalistic sample of psychotherapy patients is therefore worthwhile. Moreover, up to date hardly any confirmatory research has been conducted in this field. Strictly confirmatory research implies two major requirements: firstly, specific hypotheses, including expected effect sizes and statistical approaches to data analysis, must be detailed prior to inspection of the data, and secondly, corresponding protocols have to be published online and freely available. Here, we introduce a longitudinal naturalistic study aimed at examining, firstly, the prospective impact of baseline personality traits on the outcome of psychotherapy over a 6-month observation period; secondly, the stability and change in personality traits over time; thirdly, the association between longitudinal change in psychopathology and personality; fourthly, the agreement between self-reports and informant rating of personality; and fifthly, the predictive validity of personality self-reports compared to corresponding informant ratings. For it, we comprehensively state *a priori* hypotheses, predict the expected effect sizes and detail the statistical analyses that we intend to conduct to test these predictions. Such a stringent confirmatory design increases the transparency and objectivity of psychopathological research, which is necessary to reduce the rate of false-positive findings and to increase the yield of scientific research.

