### Instruments and Measures

Because this is a fully naturalistic study, we will use only instruments and measures that are routinely applied at the KGI to all patients. That is, to avoid methodological artifacts such as design or experimenter effects, we will not add additional assessment procedures that are not part of the basic psychotherapy evaluation. In consequence, the coverage and range of assessment instruments is limited those applied at the study site. However, note that there are further instruments applied at the KGI that are not considered in the present study, because they are administered only to selected patients with specific problems or because they were considered redundant for the present study aims. Normal-range personality will be assessed with a German adaptation (99) of the well-established Big Five Inventory (BFI) (100). The BFI is a brief self-report inventory capturing the basic structure of personality based on the broad domains of neuroticism, extraversion, openness, conscientiousness, and agreeableness. The BFI has been validated in diverse samples across nations, including English, German, Dutch, and Chinese, and is considered a reliable and valid short assessment of the FFM (99–102). Personality will be further assessed using the German adaptation (103) of the Inventory of Interpersonal Problems (IIP) (104). The IIP relies on the interpersonal circumplex model (105, 106) and captures personality difficulties based on the following eight primary domains of interpersonal problems, that is, domineering, vindictive, cold, socially avoidant, submissive, exploitable, overly nurturant, and intrusive. On a higher-order level, these domains collapse into the meta-factors of agency/dominance and communion/affiliation. The circumplex personality domains revealed strong and consistent associations with both the Big Five traits of extraversion and agreeableness and personality disorder dimensions (107–109), which is why personality pathology is considered a disorder of interpersonal behavior (110–112). In addition to the self-report IIP, an informant rating scale of the circumplex model will also be administered using the Impact Message Inventory-Circumplex (IMI-C) (113, 114). The informant rating will be provided by various sources; however, in most cases, the rater will be the partner/spouse or a family member. The BFI will be assessed at both baseline and 6-month follow-up, while IIP and IMI-C will be completed at baseline only due to their length.

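### Paper 2, hypothesis 1: self and informant are rated with different inventories, so a low IIP–IMI-C correlation is ambiguous, yet it is the predicted result

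*Protocol article*

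**What the plan says.** The Abstract gives the fourth aim as "the agreement between self-reports and informant rating of personality". In Hypotheses and Planned Analyses, second paper, hypothesis 1 makes this a prediction with a cut-off: "Self-reports and informant ratings of interpersonal personality problems are only modestly correlated (all *r* < 0.3". The test is stated in one sentence: "we will subject the IIP (self-report) and the IMI-C (informant rating) to a bivariate Pearson correlation analysis". Hypothesis 3 then has the authors "compute the index of profile agreement (*I*_pa_) between IIP and IMI-C" and treats the index as self-other agreement.

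Instruments and Measures defines the two inventories. The IIP is the self-report and "captures personality difficulties based on the following eight primary domains of interpersonal problems". On the informant side, the article says: "In addition to the self-report IIP, an informant rating scale of the circumplex model will also be administered using the Impact Message Inventory-Circumplex (IMI-C". It describes no IMI-C completed by the patient and no IIP or BFI completed by the informant. On timing, "IIP and IMI-C will be completed at baseline only due to their length".

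Correction for unreliability appears once, in the first paper's hypothesis 1 on BFI stability, where attenuated and disattenuated coefficients will both be given. None is stated for the IIP–IMI-C correlation. Caveats and Potential Pitfalls discusses content overlap that could inflate personality–psychopathology associations. It does not mention a difference between instruments that could deflate this one.

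**The concern.** A self-informant correlation shows agreement between persons most directly when both rate the same thing with the same measure. Here a correlation below 0.3 has three possible sources: the raters see the patient differently, the inventories capture partly different content, or the scales are noisy. The design has no element that separates the first from the second.

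The direction of the hypothesis makes this matter. Attenuation usually works against the claim being tested. Here the predicted result is a low correlation, so measurement weakness works for it. The article provides a correction for unreliability where unreliability opposes the prediction (BFI stability, r > 0.6) and states none where it favours the prediction. What is at stake is how hypothesis 1 and the fourth aim may be interpreted, and what the index in hypothesis 3 may be called.

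**Working it through.** There is no stated figure to reproduce: 0.3 is a chosen threshold, not a derived one. The steps below show how the threshold behaves.

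**Inputs from the article.** Threshold r < 0.3 for all correlations; eight IIP domains; about 100 six-month follow-ups, so at least about that many baselines.

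**Assumed inputs (not in the article).** True self-other agreement *a*; overlap *c*, the correlation the two inventories would show in the same rater without error; reliability *k*, the geometric mean of the two scale reliabilities. The multiplicative form is itself an assumption.

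**Step 1. Expected raw correlation**, r = a × c × k:

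| a | c | k | expected r |
|---|---|---|---|
| 0.6 | 0.6 | 0.8 | 0.288 |
| 0.6 | 0.8 | 0.8 | 0.384 |
| 0.45 | 0.7 | 0.8 | 0.252 |
| 1.0 | 0.4 | 0.7 | 0.280 |

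The first two rows have the same agreement and fall on opposite sides of 0.3. They differ only in overlap, which the plan does not measure. The last row is an extreme case: perfect agreement can still give an expected r below 0.3.

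**Step 2. Largest true agreement compatible with an expected r below 0.30**, a = 0.30 / (c × k), with k = 0.8:

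- c = 0.6: 0.30 / 0.48 = 0.625
- c = 0.8: 0.30 / 0.64 = 0.469
- c = 1 (one common instrument): 0.30 / 0.80 = 0.375

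**Step 3. What disattenuation can and cannot do.** The corrected value is r / k. With k = 0.8, a raw r from 0.24 to just under 0.30 becomes 0.24 / 0.8 = 0.30 to just under 0.30 / 0.8 = 0.375, so the reading against the threshold changes. The correction removes *k* and leaves a × c. In the first row of step 1 it gives 0.288 / 0.8 = 0.36, still well below the assumed agreement of 0.6. Instrument mismatch remains and has to be handled by wording.

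**Step 4. How likely is confirmation?** Hypothesis 1 requires every correlation to be below 0.3. Take eight matched correlations, each with expected r = 0.25, and n = 100. By Fisher z, (atanh 0.30 − atanh 0.25) × √97 = (0.3095 − 0.2554) × 9.849 = 0.533, so one correlation falls below 0.3 with probability 0.703. All eight do so with probability 0.703^8 = 0.06 if their errors are independent. With equally correlated errors the figure is about 0.29 (correlation 0.5) or 0.46 (correlation 0.8). An expected r under 0.3 therefore does not make confirmation likely.

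**Step 5. Precision.** At n = 100 an observed r of 0.20 has a 95% interval of 0.00 to 0.38 (Fisher z, standard error 1/√97), which includes values above 0.3.

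**The case against.** The strongest reply is that both inventories follow the interpersonal circumplex, that the study is restricted to routine instruments, and that the test sentence openly names which instrument goes with which rater. All of this stands. The inventories are related, and a low r carries information. But a shared model does not make them parallel forms, and the restriction to routine instruments explains the design without supporting the reading of r as agreement.

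Several stronger readings are tempting and are not supported:

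- *Hypothesis 1 would be confirmed even when raters agree well.* It could be. Step 4 shows that the requirement on all correlations makes this far from assured, and with higher overlap the hypothesis fails.
- *The fourth aim cannot be answered.* Ambiguity limits the interpretation; it does not make the correlation empty.
- *The first paper decides its threshold on the disattenuated coefficient.* It says only that both coefficients will be given. It is a precedent for reporting, not for deciding.
- *Hypothesis 3 is biased towards success.* It predicts that profile agreement relates more strongly to outcome than either inventory alone. Noise from mismatch would tend to weaken that relation and so work against it. The index follows a cited procedure that is not reproduced in the article, so whether it already standardises scores cannot be judged.
- *Results should be split by informant.* The article says "The informant rating will be provided by various sources", but a split by informant type would not separate rater from instrument.

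**Conclusion.** The point holds as a limit on interpretation. Rater and instrument are fully confounded in the second paper's hypothesis 1, and both inventory mismatch and unreliability push r in the predicted direction. A result of all r < 0.3 could thus be reported as confirmation without true self-other disagreement. This conclusion needs only that overlap is below 1 and unknown and that the scales are not perfectly reliable.

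The size cannot be given from the article. On the assumed values (reliability 0.8, overlap 0.6 to 0.8), an expected r below 0.30 is compatible with true agreement up to 0.625 to 0.469, against 0.375 with one common instrument. These figures illustrate the ambiguity; they do not estimate a bias in this study. For hypothesis 3 the consequence is one of naming: the index measures similarity of two profiles that differ in both rater and instrument.

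**What to change.** 1. In the second paper's hypothesis 1, report raw and disattenuated correlations for matched circumplex domains, as the first paper's hypothesis 1 already does for the BFI. Do not call the hypothesis confirmed if the disattenuated values reach 0.3. Since both inventories are given once, the reliabilities would have to come from internal consistency in the baseline item data, or from a stated outside source.
2. Because disattenuation does not remove instrument mismatch, word hypothesis 1 and the fourth aim as convergence between IIP self-report and IMI-C informant rating. State that r < 0.3 alone will not be read as low self-other agreement.
3. In hypothesis 3, limit the conclusion to IIP–IMI-C profile similarity.

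The cost is wording plus a reliability correction on data the study is already collecting; no instrument or visit is added. The downside is a more modest claim. The change should be fixed before analysis starts, which the article places after the target of 100 follow-ups is reached.
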